## Abstract

**Background:**

Nicotine dependence is an addictive behavioral disease facilitated by habitually smoking cigarettes. In many countries, acupuncture and auricular acupressure have attracted growing attention as complementary or alternative treatments for smoking cessation; however, there is a lack of rigorous randomized, controlled studies evaluating the combination of these two interventions specifically for smoking cessation. The aim of this study is to evaluate the efficacy and safety of using acupuncture combined with auricular acupressure (A&AA) to increase the rates of smoking cessation and ultimately reduce the rates of relapse.

**Methods:**

This is a multicentre, prospective, parallel, randomized, controlled trial. A total of 360 patients with severe nicotine dependence will be randomized into test (A&AA) or control (nicotine replacement therapy, NRT) groups. The test group will be treated with A&AA twice weekly, while the control group will use an NRT patch daily. All treatments will be administered for 8 weeks, with a follow-up period of 4 months. The primary outcome will be the smoking abstinence rate at week 24, with a combined safety assessment. The secondary outcomes will be smoking cessation rates at other timepoints, saliva cortisone test results, and scores on the Fagerstrom Test for Nicotine Dependence, the Autonomy over Tobacco Scale, the Hamilton Anxiety Rating Scale, the Self-rating Anxiety Scale, and the Pittsburgh Sleep Quality Index. The cost of treatment will also be used to evaluate the economic effects of different smoking cessation interventions. Statistical analysis on the data collected from both the intention-to-treat (all randomly assigned patients) and per-protocol (patients who complete the trial without any protocol deviations) patients, will be performed using the statistical software package, IBM SPSS 27.0.

**Discussion:**

This study will provide rigorous clinical evidence evaluating the efficacy and safety of using A&AA as a smoking cessation therapy.

**Trial registration:**

Chinese Clinical Trial Registry (Registration number: ChiCTR1900028371).

## Background

Nicotine dependence has been classified as a mental and behavioral disorder by the 2010 International Classification of Diseases codes issued by the World Health Organization. According to research published in the fields of tobacco economics and control, tobacco kills approximately six million people, costs the world's economies more than one trillion dollars annually, and remains one of the major causes of premature death (1). China has the highest rates of cigarette addiction worldwide, especially among male smokers. In China, more than one million people lose their lives each year from smoking-related diseases (2). Diseases and mortality associated with smoking pose a serious threat to public health. The high smoking rate and the difficulty in controlling this addiction suggests that key policymakers should devote significant resources to this issue. In fact, health authorities in many countries have strongly recommended that doctors intervene to help patients quit smoking.

The main methods for achieving smoking cessation are nicotine replacement therapy (NRT), antidepressant medications, and psychological counseling, with various studies confirming that these methods improve the success rate of smoking cessation to varying degrees (3, 4). Unfortunately, these therapies also have potential side effects, including chest tightness, insomnia, dry mouth, skin allergies, and gastrointestinal reactions (5–12), which can reduce patient compliance and most importantly, the efficacy of smoking cessation.

Since 2015, complementary and alternative medicine for substance use disorders has increasingly gained attention, and acupuncture may be a hotspot in this field (13). Various types of acupuncture, such as hand acupuncture, ear acupuncture, laser acupuncture, have gained attention in many countries as therapeutic interventions for smoking cessation (14). In a smoking cessation trial in Norway (15), the experimental group received an acupuncture intervention at the “Shenmen,” “Mouth,” and “Liver” acupoints of the ear, as well as at the acupuncture points, Kongzui (LU 6) and Lieque (LU 7), leading to significant changes in the taste of cigarettes and the desire to smoke, compared with the control group. A multicentre, randomized trial of 300 patients in China (16) also showed that the effects of acupuncture on smoking cessation were not inferior to NRT. Available evidence supports the acupuncture therapy have very wide popularization and application prospects in smoking cessation, while it is also suggested that single type acupuncture therapy is relatively insufficient in the long term of the abstinence rate, and the evidence is insufficient in the efficacy of combined acupuncture therapy (17–19). Thus, we carry out this RCT to observe the effect of combined acupuncture therapy on smoking cessation.

This multicentre, randomized, controlled clinical trial, which is based on a previous study of acupuncture for smoking cessation, will be the first to evaluate whether the combination of a short-term but strong stimulation, elicited by acupuncture and the long-term, milder stimulation elicited by auricular acupressure, will lead to better smoking cessation outcomes. Additionally, we hope to determine whether this treatment (A&AA) has better smoking cessation outcomes and is safer than NRT. We also hope to evaluate the benefits of A&AA from the perspective of health economics, in order to develop effective and affordable smoking cessation plans.

## Methods

### Study design

For this study, a multicentre, prospective, randomized controlled trial will be conducted to compare the effects of A&AA with those of NRT, on smoking cessation. A total of 360 patients with severe nicotine dependence, who are willing to voluntarily quit smoking, will be randomly divided into a treatment group (A&AA) or a control group (NRT). The First Affiliated Hospital of Guangzhou University of Chinese Medicine, the Hong Kong Pok Oi Hospital, and the Shenzhen Chinese Medicine Hospital will be responsible for patient recruitment, screening, interventions, and the follow-up of 280, 30, and 50 patients, respectively. All outcomes will be assessed at The First Affiliated Hospital of Guangzhou University of Chinese Medicine. Management of the randomization sequence, blinding, and data analyses, will be carried out at the Clinical Research and Data Center of Guangzhou University of Chinese Medicine. Ethical approval for this study was received from the First Affiliated Hospital of Guangzhou University of Chinese Medicine (No. ZYYECK [2019] 099), and this study will be conducted according to the Declaration of Helsinki, 7th revision (2013). Informed written consent will be obtained from all patients. The flow diagram for patient selection and methodology is shown in Figure 1. This protocol is reported in accordance with the Standard for Reporting Interventions in Clinical Trials of Acupuncture recommendations (STRICTA) (20).

**Figure 1 F1:**
[figure not shown]
Patient selection and methodological flow.

### Patients

Smokers have the intention to quit smoking and meet our following criteria will be recruited at three sites simultaneously. Posters, leaflets and WeChat advertisements will be used in the recruitment process. Formal enrollment is only considered if participants signed written informed consent.

### Inclusion criteria

Patients who meet all the following criteria will be included: (1) Meet the diagnosis of ICD-10 Nicotine Dependence; (2) between 18 and 65 years of age; (3) smoking history of ≥1 year; (4) currently smokes ≥20 cigarettes per day over the past 1 year; (5) detection of cotinine in saliva; (6) a Fagerstrom Test for Nicotine Dependence (FTND) score of ≥4; (7) willingness and ability to sign a consent form, ensuring that they understand the trial and will take part in it voluntarily; and (8) an elution period of more than 1 month for all smoking cessation therapies, including acupuncture, auricular acupressure, and NRT.

### Exclusion criteria

Patients will be ineligible to participate in this trial if they meet any of the following criteria: (1) severe heart, lung, brain, or blood system diseases or diabetes; (2) drug use or those diagnosed with mental illnesses; (3) history of stroke or nervous system diseases; (4) unexplained symptoms; (5) history of a coagulation disorder or anticoagulant drug history; (6) moderate or severe impairment of liver or kidney function; (7) pregnant or breast feeding; or (8) already using smoking cessation therapies, such as acupuncture, auricular acupressure, NRT, etc.

### Elimination criteria

Patients will be eliminated from the trial based on the following criteria: (1) patients who are willing to participate, but fail to meet the inclusion criteria, and (2) those who fail to complete instructions or procedures with obvious implications for efficacy or safety.

### Termination criteria

The trial will be terminated if the following situations occur during its course: (1) therapies exacerbate the state of the illness or lead to secondary infections; (2) external factors worsen the patients' conditions; or (3) patients are unwilling to continue the trial.

### Sample size

According to a previous randomized, controlled study of acupuncture for smoking cessation (15), we expect that the success rates for smoking cessation will be on average 44% in the NRT (control) group and 60% in the A&AA (treatment) group, using the abstinence rate for smoking cessation at week 24 (24-h carbon monoxide [CO] clearance rate of <10 parts per million) as the primary outcome. Using PASS 2008 software, the sample size required for each group was estimated to be 152 cases by two independent sample rate comparison methods.

Therefore, considering an expected loss of 15% during the follow-up period, we will recruit a total of 360 (≈304/0.85) volunteers for this study. Allocation into the two groups will be assigned in a 1:1 ratio, and each group size will be set at 180.

### Randomization and allocation

Eligible patients will be randomly assigned to receive A&AA or NRT *via* a central randomization system (Clinical Research and Data Center, Guangzhou University of Chinese Medicine). Random numbers will be generated using the stratified block method by a designer from the Clinical Research and Data Center, not involved in the study. Because of the obvious differences between the two types of therapies, blinding of patients and healers will not be possible; therefore, only outcome evaluators will be blinded to the treatment allocation.

### Interventions

Patients with chronic diseases who are taking medication can continue to take medication as prescribed by specialist doctors during the phase of this trial.

### A&AA group

Patients in this group will receive acupuncture and ear acupuncture treatment in sequence delivered by licensed acupuncturist with at least 5 years of therapeutic experience. Locations of all the acupoints are in line with the National Standard of the People's Republic of China's (GB/T 12346–2006) standard.

Manual acupuncture acupoint prescriptions include:Baihui (DU 20), Yintang (EX-HN3), bilateral Lieque (LU 7), and bilateral Hegu (LI 4) (Figure 2). The acupuncture procedure will be as follows: Before acupuncture, patients will be placed in a supine position to expose the acupoints. After skin disinfection, 40-mm disposable sterile needles will be inserted horizontally at Baihui (GV 20), bilateral Hegu (LI 4), and bilateral Lieque (LU 7, point to Yangxi), and a 25 mm needle will be inserted vertically at Yintang (EX-HN3). The neutral supplementation and draining method will be applied at all acupoints for 30 min after achieving the arrival of qi; the needle will be manipulated every 10 min to avoid discomfort (needle sensation as soreness or numbness).

**Figure 2 F2:**
[figure not shown]
Acupuncture points.

After the acupuncture procedure, auricular compression at Shenmen (TF 4), Fei (CO 14), Wei (CO 4), Neifenmi (CO 18), Pizhixia (AT 4), and Jiaogan (AH 6) (Figure 3) will be applied. The acupuncture procedure will be as follows: after routine disinfection of the auricle and ear circumference, a patch of vaccaria seeds will be stuck to the auricular acupoints mentioned above on one ear (contralateral to the ear on which this technique was performed 3-day earlier). In addition, patients will be instructed to press each auricular acupuncture point for 60 s, 3–5 times per day.

**Figure 3 F3:**
[figure not shown]
Nomenclature and location of auricular points (21).

The A&AA interventions will be performed simultaneously twice a week for a total treatment course of 8 weeks.

### NRT group

Patients in the NRT group will receive NRT patches purchased from Novartis (approval number: N07BA01) which are composed of nicotine at three different dosages, including 21, 14, and 7 mg. After removing the protective foil, the patch will be applied to a clean, dry, intact area of skin (free from lotion, alcohol, or ointment), preferably on the trunk or otherwise on the upper arm or hip, and pressed with the palm for 10 s. To avoid local irritation of the skin, a different site of application will be chosen each day. Patients will be asked to use one patch per day and visit the outpatient clinic twice per week. Treatment will start at 21 mg/d for 4 weeks, followed by 14 mg/d for 2 weeks, and 7 mg/d for the final 2 weeks. The total course of treatment will be 8 weeks.

### Strategies to improve adherence

All the therapies and medical examination items in this trial will be provided to the patients free of charge, and patients who can complete all the visits will be reimbursed the transportation expenses. These measures will improve the patients' compliance.

### Outcome measures

#### Primary outcome

The abstinence rate for smoking cessation at week 24 (number of people who quit smoking/total number of people) will be considered the primary outcome. Patients with a 24-h CO clearance rate of <10/1,000,000 at the 24th week of therapy, will be considered to have successfully quit smoking.

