#### Secondary outcomes

The secondary outcomes will be the prolonged abstinence rate, the abstinence rate at other time points, the results from a saliva cortisone test, and scores on the Fagerstrom Test for Nicotine Dependence (FTND), the Autonomy over Tobacco Scale (AUTOS), the Hamilton Anxiety Rating Scale (HAM-A), the Self-rating Anxiety Scale (SAS), and the Pittsburgh Sleep Quality Index (PSQI). Additionally, we will conduct safety assessments of and evaluate cost of treatment.

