### Assessment of adverse events

All adverse events will be reported in detail in an observation table (Table 1), including the type of event, the extent of symptoms or diseases, the date of onset, frequency, duration, the remission date, treatment measures, treatment process, results, and follow-up, for evaluation of any correlations between adverse reactions and A&AA or NRT.

**Table 1 T1:** Description of the study schedule.

**Task**	**Screening**	**Observation period**				**Follow-up period**		**Unplanned follow-up**
	**Visit 0** **Week 0**	**Visit 1** **Week 2**	**Visit 2 Week 4**	**Visit 3** **Week 6**	**Visit 4 Week 8**	**Visit 5** **Week 16**	**Visit 6 Week 24**	
Medical history collection	√	–	–	–	–	–	–	–
Signing informed consent	√	–	–	–	–	–	–	–
Inclusion criteria	√	–	–	–	–	–	–	–
Exclusion criteria	√	–	–	–	–	–	–	–
Basic information	√	–	–	–	–	–	–	–
Vital signs	√	√	√	√	√	√	√	√
Blood and urine tests	√	–	–	–	√	–	√	
Liver and kidney function	√	–	–	–	√	–	√	
Respiratory carbon monoxide determination	√	√	√	√	√	√	√	
Coagulation	√	–	–	–	√	–	√	
Blood lipids + HCY	√	–	–	–	√	–	√	
Saliva cotinine test	√	–	–	–	–	√	√	
ECG	√	–	–	–	–	–	√	
FTND	√	√	√	√	√	√	√	
AUTOS	√	√	√	√	√	√	√	
HAM-A	√	√	√	√	√	√	√	
SAS	√	√	√	√	√	√	√	
PSQI Scale	√	√	√	√	√	√	√	
Adverse event record	–	√	√	√	√	√	√	
Combined medication records	√	√	√	√	√	√	√	
Termination test evaluation	–	√	√	√	√	√	√	

*AUTOS, Autonomy over Tobacco Scale; ECG, electrocardiogram; FTND, Fagerstrom Test for Nicotine Dependence; HAM-A, Hamilton Anxiety Rating Scale; SAS, Self-rating Anxiety Scale; PSQI, Pittsburgh Sleep Quality Index.*

*“√” is recorded when necessary*.

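### Week-24 quit status rests on one CO reading labelled 24-h; the saliva cotinine scheduled at the same visit has no role in it and is called cortisone in the outcome lists

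*Protocol article*

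**What the plan says.** Protocol article, Primary outcome: "Patients with a 24-h CO clearance rate of <10/1,000,000 at the 24th week of therapy, will be considered to have successfully quit smoking". The Sample size section repeats the criterion as the basis for the expected rates: "24-h carbon monoxide [CO] clearance rate of <10 parts per million". Neither place adds a self-report condition, a longer window or a second marker.

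Table 1 (under Assessment of adverse events) has a row "Respiratory carbon monoxide determination" ticked at screening and at weeks 2, 4, 6, 8, 16 and 24, so there is one determination at the week-24 visit. It also has a row "Saliva cotinine test" ticked at screening and at weeks 16 and 24. Cotinine is used at entry as well, through the criterion "detection of cotinine in saliva".

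The outcome lists name a different analyte. The abstract has "saliva cortisone test results" and the Secondary outcomes section has "the results from a saliva cortisone test". Table 1 contains no cortisone test.

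Longer abstinence appears only as a secondary outcome: "The secondary outcomes will be the prolonged abstinence rate, the abstinence rate at other time points". The Statistical analysis section assigns the primary outcome to the ITT population and secondary outcomes to the per-protocol set. Patients and therapists are unblinded; only outcome evaluators are blinded (Randomization and allocation).

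**The concern.** As written, one CO value under 10 ppm is sufficient for success, and by the plan's own label it speaks to about a day. Visits are scheduled, so a continuing smoker who stops shortly beforehand can be counted as having quit. Blinding the evaluator does not prevent this, because the behaviour is the patient's and the patient knows the treatment. If the tendency differs between arms, the primary comparison is biased, and so is the cost-effectiveness analysis, which uses the same outcome as its effectiveness measure.

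A second marker is scheduled at the same visit, but the plan gives it no role in the abstinence definition. Its apparent place among the secondary outcomes carries the wrong name. Even with the name corrected, it would be analysed in the per-protocol set, so no confirmation of the primary result in all randomised patients is planned.

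**Working it through.** **1. The definition beside the schedule.**

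| Item | Where | Content |
|---|---|---|
| Quit rule | Primary outcome; Sample size | CO below 10 ppm, labelled 24-h, at week 24 |
| CO at week 24 | Table 1 | one determination |
| Saliva cotinine | Table 1 | screening, weeks 16 and 24 |
| Saliva cortisone | Abstract; Secondary outcomes | listed as an outcome, absent from Table 1 |
| End of patches | NRT group | week 8 |
| Combined medication record | Table 1 | every visit |

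The gap between the last trial patch and the week-24 cotinine sample is 24 − 8 = 16 weeks, so trial patches should not explain a positive result. Nicotine products used outside the protocol could, and the combined medication record is the place to find them.

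**2. The plan's own sample size.** Inputs: p1 = 0.44, p2 = 0.60, difference 0.16, mean 0.52. Two-sided α = 0.05 and 80% power are assumed, since the article does not state the power or fix the side of the primary test.

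n = [1.960·√(2·0.52·0.48) + 0.842·√(0.44·0.56 + 0.60·0.40)]² / 0.16² = 151.9, rounded up to 152 per group.

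This matches the stated 152. For dropout, 304/0.85 = 357.6, consistent with 360. The sample size is sound on its own inputs.

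**3. Can the effect of false quits on power be derived?** Let f be the share of continuing smokers who pass the CO rule, equal in both arms. Then observed rate = p + f(1 − p). The document gives no f; 5%, 10% and 20% are assumptions. Power is two-sided 0.05, pooled, at 152 per group.

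*Reading A: 44% and 60% are true quit rates.*

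| f | Observed rates | Difference | Power |
|---|---|---|---|
| 0 | 44.0 / 60.0% | 16.0 | 80% |
| 5% | 46.8 / 62.0% | 15.2 | 76% |
| 10% | 49.6 / 64.0% | 14.4 | 72% |
| 20% | 55.2 / 68.0% | 12.8 | 63% |

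*Reading B: 44% and 60% are CO-defined rates, as the Sample size section says.* Power for the CO rule stays at 80%. Solving backwards, true rate = (observed − f)/(1 − f):

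| f | True rates | Difference | Power on true rates |
|---|---|---|---|
| 5% | 41.1 / 57.9% | 16.8 | 84% |
| 10% | 37.8 / 55.6% | 17.8 | 88% |
| 20% | 30.0 / 50.0% | 20.0 | 95% |

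*Reading C: a stricter definition lowers both CO-defined rates by the same factor.*

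| Factor | Rates | Power |
|---|---|---|
| 0.9 | 39.6 / 54.0% | 71% |
| 0.8 | 35.2 / 48.0% | 62% |
| 0.7 | 30.8 / 42.0% | 53% |

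Readings B and C both start from CO-defined rates and move power in opposite directions. The document does not say which applies.

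**4. Differential misclassification, illustration only.** Take a true rate of 44% in both arms and false quits in one arm only. The spurious difference is f × 0.56: 2.8 points at f = 5% and 5.6 points at f = 10%. The document does not indicate which arm, if either, would be affected.

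**The case against.** The primary outcome is an objective biochemical measure read by blinded evaluators. Prolonged abstinence is already a secondary outcome, and CO is measured at every visit. The phrase about 24-h clearance is unclear, since a clearance rate is not a concentration in ppm. It could stand for a 24-hour abstinence question confirmed by CO, and the full protocol may spell this out. All of this stands, and it limits the point to clarification and an added analysis.

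Three stronger readings do not hold.

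- A reader might infer that false quits cost this trial power, from 80% down to 76%, 72% or 63%. That treats 44% and 60% as true quit rates. The Sample size section gives them as rates under the CO rule, so any false quits are already inside them and the plan does not suffer that loss.
- A reader might infer that the primary outcome should be replaced. Recruitment had run for 10 months when the article was written and the trial is registered. A new primary rule would add unblinded self-report and could class patients already followed differently from later ones. A separate, more lenient track for users of nicotine products could itself apply unequally to the arms. The document does not make that case.
- A reader might infer that the biochemical secondary outcome cannot be analysed. The inclusion criteria and Table 1 make the intended analyte fairly clear, so this is a naming error to correct, although that cotinine was meant remains an inference.

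The remaining gap is that prolonged abstinence has no stated window in the article, and no planned analysis confirms the week-24 CO result with cotinine in all randomised patients.

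**Conclusion.** The point holds as a weakness of the outcome definition that can be reduced at little cost. A single CO value with a 24-h label decides the primary outcome of an open-label trial; the cotinine result due at the same visit is unused in that decision and misnamed in both outcome lists. The sample size reproduces and is not in question.

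No size or direction can be put on the bias or on any change in power, and the tables above are illustrations. The value of cotinine here rests on two assumptions. The first is that it reflects exposure over a longer period than the CO reading, which the article does not state. The second is that the scheduled samples are taken from every patient: the footnote to Table 1 says the ticks apply when necessary, so the sponsor should confirm this.

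**What to change.** 1. Keep the CO-based primary outcome. Restate it as an exhaled-CO concentration below 10 ppm at the week-24 visit, and say what period of abstinence it is meant to represent.
2. Before any look at results by arm, add week-24 abstinence confirmed by CO below 10 ppm and saliva cotinine below the assay cut-off, as the first key secondary or sensitivity analysis. Analyse it in all randomised patients rather than the per-protocol set.
3. State one rule, identical in both arms, for a positive cotinine result when the combined medication record shows use of a nicotine product.
4. Replace cortisone with cotinine in the abstract and in the Secondary outcomes section.

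Cost: wording only, with no new visit or sample if cotinine is collected as scheduled. The confirmed rates can only equal or fall below the CO-only rates, and the trial is not sized for them, so this analysis should be reported as an estimate with its confidence interval.
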